#### Education programme and supervision of the occupational therapists (OTs) in the intervention delivery of the SEE 1.0

The purpose of the education programme is to ensure that the SEE is provided as intended in a uniform and standardised way by the OTs. The education programme is based on a comprehensive intervention guide and several recorded videos, covering the foundation of SEE: (a) background of the need for new Internet-based solutions in the late phase of rehabilitation; (b) summary of empirical findings of changes in engagement in daily activities in persons with stroke, e.g. [3–5, 8, 10, 12]; (c) summary of occupational therapy theories about human daily activities [14, 59–61]; (d) person-centeredness [62–65], self-management [67, 68] and flipped classrooms [74]; (e) motivating interviewing [72]; and (f) management strategies in daily activities [27]. The intervention guide includes detailed information about programme goals, the different modules and the procedures the OTs are expected to undertake to guide their clients after each module.

The education programme is delivered in a flipped-classroom manner [74]. In addition to the educational videos, it includes information about the material for self-tutorials (including the intervention guide) with subsequent workshops to clarify issues related to the implementation and delivery of the programme in the platform and through online sessions. Additionally, during the intervention period, the OTs will receive supervision from the research group to clarify questions that arise related to the implementation of the intervention.

### Participant timeline

Enrolment of the 30–40 client participants begun in November 2020 and is expected to be completed by June 2022. Due to the person-centred format of the programme, involving a change process, the length of the intervention process with the OTs is expected to vary between 3 and 5 months. However, the participants’ change process is expected to continue up to 1 year after the intervention started [84], which explains why outcome measures will be conducted up to 12 months after starting the intervention.

The outcome measures and sociodemographic data will be conducted at baseline before the programme is initiated (0 months), and outcome measures will be further conducted at 4 and 12 months after the intervention starts. The feasibility registration forms and logbooks will be completed by the OTs for each client participant after each session throughout the intervention process. The study-specific feasibility questionnaires will be collected from the client participants after 4 and 12 months. The individual interviews with the clients will be conducted 1 and 4 months after entering the SEE. Focus group interviews with OTs will be performed on three to four occasions scheduled at random times during the study period. The focus groups with the management and other keypersons/stakeholders will occur one to two times after the intervention has been completed.

### Sample size

As this is a feasibility study, no power calculation is required [41, 85]. The sample size justification is instead based on the premises that the sample has to be sufficiently large to provide enough detail and information on the intervention. That is, on the aspects of feasibility investigated and potential outcomes [41]. It is important that the sample is representative of the target population. Additionally, as the OTs will become experienced in applying the new programme and providing Internet-based interventions the required sample size is estimated to be 30–40 clients with stroke.

### Recruitment procedures, including informed consent

The screening of potential participants will be conducted in two steps: first based on the information in the potential participant’s register and second on evaluation of their current status. Initially, staff at the rehabilitation clinics will identify potential clients based on the inclusion (diagnosis, age, time since illness, ability to express themselves orally and in writing) and exclusion criteria (other health conditions). Potential clients are sent an information letter and asked to respond whether they are interested to participate. If responses are not received within 1–2 weeks, the potential participants will be contacted by telephone to ensure that no volunteers are missed. The potential clients who show interest in participating will provide consent for their contact information to be transferred from the clinic to the researchers. Thereafter, the researchers will contact the participants by telephone and repeat the information presented in the information letter orally and respond to any questions. The participants are also informed about possible risks and benefits of participation (as stated in ethical considerations) and about the right to withdraw at any time without explanation. If written consent is given, the participants will be further screened for eligibility criteria, and the second screening step will be booked as an e-meeting (video call) to finally determine whether the participant is representative of the target population. During the screening, assessment tools will be used to evaluate whether the participants meet the criteria for the severity of disability [86], have access to a screen/computer, Internet and e-ID and can use them, not have an ongoing depression [87], experience limitation of engagement in daily activities and are motivated to undergo a change process at that time [70, 71].

The recruitment of the OTs will be based on those who are involved with the clients. Additionally, different managers and other keypersons/stakeholders in organisations related to health care and social services will be included in a “reference panel” of 5–8 persons. The staff will receive an information letter about the study with an opportunity to give their written informed consent to participate or decline without explanation.

### Outcomes and data collection methods

#### Feasibility of the intervention

Study-specific feasibility registration forms and intervention logbooks will be used to collect data about the implementation of the programme (feasibility: acceptability, adherence and value). These will be completed by the OTs after each client session during the entire intervention process.

The feasibility registration forms contain questions about delivery, compliance, dose and reach of the intervention to detect deviation in relation to the intervention guide for each client. In the intervention log books, field notes will be recorded regularly about how each client manages to use the Internet programme and implement strategies for change. Furthermore, the notes will include how the (online) therapeutic relationship and communication are working as well as unintended harms. OTs will also make notes about their own experiences of using SEE. These data will be complemented by focus group interviews with the OTs who provide the intervention. The interviews will cover experiences with SEE, such as the mode of delivery, dose, content and logic order of the modules, barriers and therapeutic components, and whether expected changes occur or not. The interviews will also cover how thoroughly the intervention guide was followed and whether the education received prior to starting the programme prepared them sufficiently to support the clients in their change processes.

A study-specific questionnaire concerning the acceptability and value of SEE from the clients’ perspective will also be collected. The questions will cover experiences of the satisfaction with intervention, such as the mode of delivery, dose, content of the modules, therapeutic relationship and communication online, as well as unintended harms and the extent to which the intended outcomes/benefits of the SEE are achieved. The clients self-report their satisfaction of the various aspects of the intervention on a 4-point ordinal scale ranging from not at all satisfied to very satisfied and the benefits of the intervention on 4-point ordinal scale ranging from do not agree at all to strongly agree.

The reference panel will take part in focus groups to identify whether SEE can be transferred and implemented in clinical practice and clinics in other contexts. This data collection will be based on process evaluation [44] that can be conducted in parallel with the intervention to investigate implementation, the role of context and mechanisms of impact.

#### Experienced changes

To determine the experiences of the intervention, qualitative research interviews [88] will be performed with a purposeful selection of the client participants. The purposive selection process [89] will continue until a variety of experiences occurs, ensuring that richness in data is achieved. The interviews will be semi-structured and conducted on two occasions during the intervention process. The questions capture experiences of the intervention/rehabilitation process and how the process influences everyday life. Questions will specifically focus on how they adopt self-initiated management strategies to overcome or prevent challenges in their engagement in daily activities, possibilities and hindrances in the process of recreating an active everyday life. The initial interview also explores the experiences of changes in engagement in daily activities and management strategies used before participating in the intervention as well as potential new insights into needed changes after the first weeks in the intervention. During the interviews, techniques that enhance the validity of interviews of people with cognitive impairments will be used [90]. The interviews will be recorded and transcribed verbatim transcribed verbatim without violating confidentiality.

#### Potential SEE outcomes

The potential outcomes of SEE will be determined using the following standardised assessment tools; The Profiles of Occupational Engagement [91] is based on an interview of a 24-h completed diary of time use. The nine items are scored on an ordinal scale and a higher score indicate a higher level of engagement in daily activities. The Occupational Balance Questionnaire (OBQ) [92] consist of 11 items that are summed to a total score, ranging between 0 and 33. A higher score implies more satisfaction with the amount and variation of occupations, i.e., a higher level of occupational balance. The Occupational Value predefined (Oval-Pd) [93] includes18 items that are summed into a general occupational value, ranging between 18 and 72. A higher score indicates that the respondent is frequently engaged in valued daily activities. The Life Satisfaction Questionnaire (Lisat-11) [94, 95] consist of 11 items, including self-reports of satisfaction with life as a whole and physical and mental health. The items are rated on ordinal scale ranging from 1 to 6 and a higher score reflect a higher level of satisfaction. How self-management is realised will be assessed using the General Self-Efficacy Scale (GSE) [96, 97] that includes 10 items that are summarized to a score ranging between 10 and 40. A higher score reflects greater sense of general self-efficacy. Actual and perceived work ability will be evaluated for those of working age. The Work Ability Index (WAI) [98] examines self-perceived work ability on a 10-point ordinal scale. A higher score reflects a higher level of perceived work ability. Goal achievement in the activity plan will be noted by the OTs.

Sociodemographic data will be collected using a registration form. To evaluate aspects of the medical disorder, the Glasgow Outcome Scale Extended (GOSE) [86], Mental Fatigue Scale (MFS) [99] and Hospital Anxiety and Depression Scale (HAD) [87] will be used at baseline.

### Data management

All the data will be transferred by the research group to a word processing or calculation computer programme and securely saved anonymously at the data storage service of Luleå University of Technology, Sweden, according to the rules and guidelines for research ethics [100, 101] and the GDPR [102]. The names, contact information and consent forms will be stored on paper, together with their identification (ID code) number, in a cabinet separate from the data to make it impossible to identify persons*.*

### Analysis

#### Feasibility of the intervention

The feasibility registration forms and study-specific questionnaires will be analysed using descriptive statistics and quantitative content analysis [103] to outline the delivery, compliance, dose, reach of the intervention, adherence and values. The intervention log books, including field notes and transcribed focus group interviews with OTs, will be analysed using qualitative content analysis [104] and the acceptability, adherence and values of SEE will be described. Additionally, the clients’ experiences of acceptability and adherence will be analysed using qualitative content analysis. The data from the focus groups with the reference panel of managers and key stakeholders will be analysed to reveal the contents and meanings inherent in the discussions of acceptability in a wider context [105]. To identify whether the assessment tools are appropriate to measure changes that may occur after SEE, the match between the experienced values and meanings of the intervention from the clients’ perspective (study-specific feasibility questionnaires, registration forms) and the outcomes identified by the assessment tools used will be compared descriptively by content analysis.

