## Abstract

**Background:**

Rehabilitation after stroke seldom focuses on needs related to an active everyday life and the process of change that people must undergo to adapt to an altered capacity and life situation. In particular, occupational therapy in the late phase needs to support clients in adopting sustainable self-initiated management strategies to regain daily activities and an active everyday life. To improve access to rehabilitation, the use of digital solutions has been suggested. *This study aims* to evaluate the feasibility of the Internet-based occupational therapy intervention “Strategies for Empowering activities in Everyday life” (SEE, version 1.0). We will investigate the feasibility of the intervention process in terms of acceptability and adherence as well as the most suitable outcome measures to evaluate SEE and improve the knowledge about the potential changes and outcomes of SEE for clients with stroke.

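### The analysis meant to judge whether the assessment tools suit SEE counts therapist-completed forms as the clients' perspective, and its content analysis can judge a tool's relevance but not its responsiveness

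*Protocol article*

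**What the plan says.** The Abstract makes it an aim to investigate "the most suitable outcome measures to evaluate SEE", and the second objective repeats this for change at 4 and 12 months. The analysis assigned to the question is in Analysis, Feasibility of the intervention. Its purpose is given as "To identify whether the assessment tools are appropriate to measure changes that may occur after SEE". The method is to match what the intervention meant to clients with what the tools show: the clients' "perspective (study-specific feasibility questionnaires, registration forms) and the outcomes identified by the assessment tools used will be compared descriptively by content analysis".

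On the registration forms, Participant timeline says: "The feasibility registration forms and logbooks will be completed by the OTs for each client participant after each session throughout the intervention process". The data collection section agrees ("These will be completed by the OTs after each client session during the entire intervention process") and gives their content: "The feasibility registration forms contain questions about delivery, compliance, dose and reach of the intervention to detect deviation in relation to the intervention guide".

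On the client questionnaire, the data collection section says that clients rate satisfaction, and also "the benefits of the intervention on 4-point ordinal scale ranging from do not agree at all to strongly agree". Participant timeline adds: "The study-specific feasibility questionnaires will be collected from the client participants after 4 and 12 months".

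Analysis, Potential SEE outcomes, separately plans descriptive statistics and non-parametric tests of change from baseline to 4 and 12 months on six tools (POES, OBQ, Oval-pd, LiSat-11, GSE and WAI), together with goal achievement.

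**The concern.** There are two linked problems.

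**Source.** One of the two inputs named for the clients' perspective is recorded by the people who deliver the intervention, and its purpose is to detect departures from the intervention guide. A match between that material and the scale results says little about whether the scales capture what clients themselves experienced.

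**Method.** Whether a tool is appropriate for measuring change has at least two parts: does its content cover what matters to clients (relevance), and does its score move when clients change (responsiveness)? Content analysis answers the first. The stated purpose is about measuring change, so it needs the second as well.

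The Discussion says that favourable results will lead to a pilot RCT. If the outcome measures for that trial are chosen on relevance alone, a tool that covers the right topics but hardly responds could be carried forward.

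**Working it through.** The article gives no figure to reproduce for this point. The check is a comparison of sections, followed by an illustration of what the planned sample could support.

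**1. Who speaks in each source**

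| Source | Completed by | Content | Named in the tool-appropriateness comparison? |
|---|---|---|---|
| Feasibility registration forms | OTs, after each session | Delivery, compliance, dose, reach | Yes, as clients' perspective |
| Study-specific questionnaire | Clients, 4 and 12 months | Satisfaction and benefit, 4-point ordinal items | Yes, as clients' perspective |
| Individual interviews | Purposive subset of clients, 1 and 4 months | How the process affects everyday life, strategies adopted | No |

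The only other registration form in the article, under Potential SEE outcomes, collects sociodemographic data. Reading the term that way does not supply clients' experienced values either. The source label is therefore wrong on either reading.

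**2. What each planned analysis can show**

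- The content-analytic match can show whether a tool's content overlaps with what clients value. No numerical link to individual score change is stated.
- The tests under Potential SEE outcomes can show whether scores shift within the group. They are not linked to client-reported benefit or to tool choice. The design has no control group, so a null result could mean no change or an insensitive tool, and a positive result could reflect any drift from pretest to posttest.

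Neither analysis, as stated, relates score change to whether the client reports benefit. The benefit items and the follow-up scales are both collected at 4 and 12 months, so the data for that link exist.

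**3. What the link could deliver with 30–40 clients**

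Inputs: n = 35 is the midpoint of the stated 30–40. The correlations r between individual change and a benefit rating are assumptions. Follow-up is taken as complete.

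Formula (Spearman, Fisher z): atanh(r) ± 1.96 × √[(1 + r²/2)/(n − 3)], then back-transformed with tanh.

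- r = 0.5, n = 35: SE = √(1.125/32) = 0.1875, half-width 0.3675. The range 0.5493 ± 0.3675 is 0.182 to 0.917, which gives **0.18 to 0.72**.
- r = 0.3, n = 35: SE = √(1.045/32) = 0.1807, half-width 0.354. The range 0.3095 ± 0.354 is −0.045 to 0.664, which gives **−0.04 to 0.58**.

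At the ends of the planned range:

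| r (assumed) | n = 30 | n = 40 |
|---|---|---|
| 0.3 | −0.08 to 0.60 | −0.02 to 0.56 |
| 0.5 | 0.15 to 0.74 | 0.20 to 0.71 |
| 0.7 | 0.42 to 0.86 | 0.47 to 0.84 |

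At n = 35 the intervals are 0.72 − 0.18 = 0.54 wide for r = 0.5 and 0.58 + 0.04 = 0.62 wide for r = 0.3, and they overlap over most of their length. A clearly responsive tool can be told from zero. Tools with similar responsiveness cannot be put in order.

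**The case against.** The strongest reply is that the article does address change on every tool: Potential SEE outcomes plans descriptive statistics and tests at both follow-ups. The content comparison then adds relevance, for which content analysis is a suitable method. That stands, and it limits the point. A reader might infer that the protocol has no way to see whether a tool registers change. It has one, but that analysis is not tied to client-reported benefit or to the choice of tools.

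Three other stronger readings are tempting, and the text does not support them.

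- *The comparison is made only at group level.* The article does not state the level. The questionnaires come from individual clients, and the forms are completed per client.
- *Tools will be chosen by which p-value falls below 0.05.* Nothing says so. The tests are not connected to tool selection at all.
- *The study undertakes to rank six tools.* It asks whether the tools are appropriate. They measure different constructs, so ranking them on one anchor would be questionable even with a larger sample.

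It is also fair to say that standardised response means and floor or ceiling shares are details an article may leave to a fuller document. Their absence is not the fault here; they are offered as useful companions to the main change. The interviews, too, have limits: they cover a purposive subset, stop at 4 months and have their own grounded-theory analysis. They can inform the comparison qualitatively but cannot speak to 12 months.

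Finally, the questionnaire has several questions on benefit, and the article describes no single global rating. Any anchor has to be defined before it is used.

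None of this touches the mislabelled source, or the gap between the stated purpose and the method assigned to it.

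**Conclusion.** The point holds in two parts.

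1. The article contradicts itself on the source. The registration forms are OT-completed delivery data and do not carry the clients' perspective. This rests on the text alone.
2. The only analysis tied to whether the tools are appropriate for measuring change can assess relevance but not responsiveness. The separate tests of change do not fill the gap, because they are unlinked to perceived benefit and uncontrolled.

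The gain from repairing the second part is real but modest. On the assumptions of 35 clients and full follow-up, a correlation of 0.5 would be estimated as about 0.18 to 0.72, while one of 0.3 could not be told from zero. Losses by 12 months would widen these intervals. WAI is collected only from clients of working age, so its interval will probably be wider still. It would be wrong to infer that the sample can separate responsive from unresponsive tools in general, because the intervals for r = 0.3 and r = 0.5 overlap heavily.

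The change is worth making before analysis. It does not call the conduct of the study into question.

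**What to change.** - **Sources.** Take the OT registration forms out of the clients' perspective, or keep them under the label of the OT perspective. Add the client interviews as a qualitative source, noting that they come from a purposive subset at 1 and 4 months.
- **Relevance.** Keep the content analysis for this purpose, and say so.
- **Responsiveness.** For each tool, at 4 and at 12 months, report the Spearman correlation with 95% CI between individual change from baseline and the client's own benefit rating. State in advance which item, or which summary of the 4-point benefit items, is the anchor. Report the standardised response mean and the share of clients at floor and ceiling alongside.
- **Presentation.** Show these figures next to the qualitative themes for each tool, with the number of clients contributing. Describe them as indicative, and do not rank closely placed tools.

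The cost is a change of wording in the analysis section and a small amount of extra analysis on data already planned. No new visits or instruments are needed. The drawback is that the estimates will be imprecise and must be reported as such.
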